## 2 STUDY OBJECTIVES

The primary objective of the Wü-KiTa-CoV study is to evaluate various alternative surveillance programmes for the detection of SARS-CoV-2 cases in daycare centers with respect to their acceptability and practical feasibility. In addition, the study aims to analyse potential predictors of acceptability and the psychosocial effects of the permanent monitoring on children, families and childcare workers. The study is furthermore intended to provide initial data on relevant cost factors associated with the different surveillance protocols.

Depending on data availability, the study will, in addition, provide initial data on the detection of SARS-COV-2 cases and seroprevalence data in children attending daycare centers in the Würzburg area.

### 2.1 Primary Hypotheses

- [1] Screening of asymptomatic children and childcare workers in daycare centers for SARS-CoV-2 using mid-turbinate swabs twice or once a week will be accepted with dropout rates remaining below a level of relevance for the respective testing frequency.
- [2] Screening of asymptomatic children and childcare workers in daycare centers for SARS-CoV-2 by saliva samples to be handed in twice a week will be accepted without resulting in a relevant dropout rate.
- [3] Surveillance by symptom-based testing for SARS-CoV-2 of household members of children or childcare workers in daycare centers using oropharyngeal swabs will be accepted without resulting in a relevant dropout rate.

(For primary endpoints and definitions cf. Chapter 7.1)

### 2.2 Secondary Hypotheses

- [1] Monitoring for SARS-Cov-2 carried out in daycare centers twice [once] a week using mid-turbinate swabs/saliva samples leads to an increased sense of security and satisfaction amongst the children, their families and the childcare workers.
- [2] Surveillance by symptom-based testing for SARS-CoV-2 of household members of children or childcare workers in daycare centers using oropharyngeal swabs leads to an increased sense of security and satisfaction amongst the children, their families and the childcare workers.

### 2.3 Study design und time schedule

#### 2.3.1 Design

Feasibility study (open, multicentre longitudinal intervention study)

### 2.3.2 Time schedule

After the end of the summer holidays 2020, childcare workers and parents in the selected daycare centers will be provided with information material and their informed consent will be sought. Implementation of the surveillance modules will begin as soon as possible after the end of the summer holidays, with the requirement of a simultaneous start in all daycare centers and modules. The implementation of the modules in the daycare centers will last at least 12 weeks and is expected to end with the start of the Christmas holidays.

| Year                                                                                                            | 2020 |    |    |    |   |   |   |   |   |   |   |   | 2021 |    |    |    |    |    |    |    |    |    |    |    |    |    |    |    |    |    |    |    |    |    |    |
|-----------------------------------------------------------------------------------------------------------------|------|----|----|----|---|---|---|---|---|---|---|---|------|----|----|----|----|----|----|----|----|----|----|----|----|----|----|----|----|----|----|----|----|----|----|
| Month                                                                                                           | J    | J  | J  | A  | A | A | A | S | S | S | S | O | O    | O  | O  | N  | N  | N  | D  | D  | D  | D  | J  | J  | J  | J  | J  | F  | F  | F  | F  | M  | M  | M  |    |
| Calendar week                                                                                                   | 28   | 29 | 30 | 31 | 1 | 2 | 3 | 4 | 5 | 6 | 7 | 8 | 9    | 10 | 11 | 12 | 13 | 14 | 15 | 16 | 17 | 18 | 19 | 20 | 21 | 22 | 23 | 24 | 25 | 26 | 27 | 28 | 29 | 30 | 31 |
| Preparation                                                                                                     |      |    |    |    |   |   |   |   |   |   |   |   |      |    |    |    |    |    |    |    |    |    |    |    |    |    |    |    |    |    |    |    |    |    |    |
| Planning meeting with local health authority, childcare centres' sponsoring institutions, Würzburg City Council |      |    |    |    |   |   |   |   |   |   |   |   |      |    |    |    |    |    |    |    |    |    |    |    |    |    |    |    |    |    |    |    |    |    |    |
| Finalisation of study protocol, participant information / informed consent forms                                |      |    |    |    |   |   |   |   |   |   |   |   |      |    |    |    |    |    |    |    |    |    |    |    |    |    |    |    |    |    |    |    |    |    |    |
| Ethics committee approval (preparation of documents, application process)                                       |      |    |    |    |   |   |   |   |   |   |   |   |      |    |    |    |    |    |    |    |    |    |    |    |    |    |    |    |    |    |    |    |    |    |    |
| Recruitment of study personnel (physician, study nurse, medical students)                                       |      |    |    |    |   |   |   |   |   |   |   |   |      |    |    |    |    |    |    |    |    |    |    |    |    |    |    |    |    |    |    |    |    |    |    |
| Specification of standard operating procedures, training for study team                                         |      |    |    |    |   |   |   |   |   |   |   |   |      |    |    |    |    |    |    |    |    |    |    |    |    |    |    |    |    |    |    |    |    |    |    |
| Information session/material for childcare centres' sponsoring institutions                                     |      |    |    |    |   |   |   |   |   |   |   |   |      |    |    |    |    |    |    |    |    |    |    |    |    |    |    |    |    |    |    |    |    |    |    |
| Setting up of central study office, administrative database, organisation of laboratory services                |      |    |    |    |   |   |   |   |   |   |   |   |      |    |    |    |    |    |    |    |    |    |    |    |    |    |    |    |    |    |    |    |    |    |    |
| Recruitment of study centres                                                                                    |      |    |    |    |   |   |   |   |   |   |   |   |      |    |    |    |    |    |    |    |    |    |    |    |    |    |    |    |    |    |    |    |    |    |    |
| Data collection questionnaires / interviews                                                                     |      |    |    |    |   |   |   |   |   |   |   |   |      |    |    |    |    |    |    |    |    |    |    |    |    |    |    |    |    |    |    |    |    |    |    |
| Lists of costs, drop out lists                                                                                  |      |    |    |    |   |   |   |   |   |   |   |   |      |    |    |    |    |    |    |    |    |    |    |    |    |    |    |    |    |    |    |    |    |    |    |
| Initial questionnaire and psychosocial questionnaire                                                            |      |    |    |    |   |   |   |   |   |   |   |   |      |    |    |    |    |    |    |    |    |    |    |    |    |    |    |    |    |    |    |    |    |    |    |
| Interviews                                                                                                      |      |    |    |    |   |   |   |   |   |   |   |   |      |    |    |    |    |    |    |    |    |    |    |    |    |    |    |    |    |    |    |    |    |    |    |
| Data collection laboratory data                                                                                 |      |    |    |    |   |   |   |   |   |   |   |   |      |    |    |    |    |    |    |    |    |    |    |    |    |    |    |    |    |    |    |    |    |    |    |
| Seroprevalence testing                                                                                          |      |    |    |    |   |   |   |   |   |   |   |   |      |    |    |    |    |    |    |    |    |    |    |    |    |    |    |    |    |    |    |    |    |    |    |
| Throat swabs modules 1-4                                                                                        |      |    |    |    |   |   |   |   |   |   |   |   |      |    |    |    |    |    |    |    |    |    |    |    |    |    |    |    |    |    |    |    |    |    |    |
| Data management                                                                                                 |      |    |    |    |   |   |   |   |   |   |   |   |      |    |    |    |    |    |    |    |    |    |    |    |    |    |    |    |    |    |    |    |    |    |    |
| Entry of data paper based / electronic questionnaires / lists                                                   |      |    |    |    |   |   |   |   |   |   |   |   |      |    |    |    |    |    |    |    |    |    |    |    |    |    |    |    |    |    |    |    |    |    |    |
| Entry of interview data                                                                                         |      |    |    |    |   |   |   |   |   |   |   |   |      |    |    |    |    |    |    |    |    |    |    |    |    |    |    |    |    |    |    |    |    |    |    |
| Entry of laboratory data microbiology and virology                                                              |      |    |    |    |   |   |   |   |   |   |   |   |      |    |    |    |    |    |    |    |    |    |    |    |    |    |    |    |    |    |    |    |    |    |    |
| Data linkage biometry, data checks                                                                              |      |    |    |    |   |   |   |   |   |   |   |   |      |    |    |    |    |    |    |    |    |    |    |    |    |    |    |    |    |    |    |    |    |    |    |
| Finalisation of database                                                                                        |      |    |    |    |   |   |   |   |   |   |   |   |      |    |    |    |    |    |    |    |    |    |    |    |    |    |    |    |    |    |    |    |    |    |    |
| Statistical analyses and report                                                                                 |      |    |    |    |   |   |   |   |   |   |   |   |      |    |    |    |    |    |    |    |    |    |    |    |    |    |    |    |    |    |    |    |    |    |    |
| Study report                                                                                                    |      |    |    |    |   |   |   |   |   |   |   |   |      |    |    |    |    |    |    |    |    |    |    |    |    |    |    |    |    |    |    |    |    |    |    |
| Publication                                                                                                     |      |    |    |    |   |   |   |   |   |   |   |   |      |    |    |    |    |    |    |    |    |    |    |    |    |    |    |    |    |    |    |    |    |    |    |
| Documentation of records, deregistration of study at ethics committee                                           |      |    |    |    |   |   |   |   |   |   |   |   |      |    |    |    |    |    |    |    |    |    |    |    |    |    |    |    |    |    |    |    |    |    |    |

### **3 STUDY POPULATION**

#### **3.1 Selection of participating centers**

The study aims to include between 7 and 11 of the approximately 80 daycare centers located in the town of Würzburg for a study period of 12 weeks. For logistical reasons, larger daycare centers ( $\geq 50$  children) will be included preferentially. The selection of daycare centers will be carried out in cooperation with the office for youth, family and social affairs at Würzburg City Council using the following selection criteria:

...for the daycare centers in which modules 1 and 2 will be implemented:

- one daycare centre each, with a minimum of 100 children cared for at the centre and a minimum of 5 childcare workers
- consent of daycare centre's management to implementation of the study

...for the 1-3 daycare centers in which module 3 will be implemented:

- daycare centers with a minimum of 50 children of age  $\geq 2$  years cared for per centre (at least 175 children across all centers) and a minimum of 5 childcare workers per centre (at least 10 across all centers)
- consent of daycare centre's management to implementation of the study

... for the daycare centers in which module 4 will be implemented:

- between 4 and 6 daycare centers with a minimum of 250 children cared for and a minimum of 25 childcare workers across all centers
- consent of daycare centre's management to implementation of the study

#### **3.2 Inclusion criteria for participants in the daycare centers**

- Children aged 1-8 years attending one of the selected daycare centers in Würzburg; childcare workers at the daycare centers; in module 4: in addition, household members of the children and childcare workers
- Written declarations of consent by both parents/guardians to sample collection, written declaration of consent by at least one parent/guardian to questionnaires/interviews, written declaration of consent by adult participants capable of giving consent (childcare workers, household members where relevant in module 4)

#### **3.3 Exclusion criteria for participants in the daycare centers**

- Missing written consent
- Module 3: Children aged  $<2$  years at the time of the start of the study

## 4 STUDY PROCESS

### 4.1 Recruitment of study centers and participants

The study will be carried out in selected daycare centers in Würzburg. The selection of daycare centers will be carried out in close cooperation with the office for youth, family and social affairs at Würzburg City Council after prior consultation with the centre's management and, where relevant, the centre's sponsoring institution. The initial selection of daycare centers will be independent of the sponsoring institutions in charge. In preparation for the study, potentially suitable daycare centers were selected beforehand and introductory information on the intended study was provided to the centers' managers. The selection criteria for daycare centers are stated in Chapter 3.1. Following consent by the centre's management, all selected daycare centers will be asked to fill in a short questionnaire regarding the structure and organisation of the daycare centre (number of children cared for, number of childcare workers, number of groups, group sizes, childcare workers per group, number of rooms, overall floor area of daycare centre, hygiene checklists specific to SARS-CoV-2).

The overall aim is to achieve participation of all children and childcare workers at each participating daycare centre as far as possible. Recruitment of only a subgroup of children or groups would be problematic due to interactions between children and groups, the shared use of communal spaces and the potential effect of individual participants being stigmatised.

The aim is to implement the study at 7-11 daycare centers in the town of Würzburg for the full duration of 12 weeks. Respiratory sample collection will not begin until the intended number of study centers have been recruited. This serves to ensure that respiratory sample collection can take place within the same 12-week period at all participating daycare centers, as warranted by the highly dynamic pattern of SARS-CoV-2 infections.

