### 4.2 Informed Consent Process

After the consent of the daycare centre's management and sponsoring institution to implementation of the study has been obtained, all children's families and all childcare workers will receive information material and informed consent forms pertaining to the intended study and the specific module to be carried out in their daycare centre. The documents will be distributed by e-mail by the daycare centre's management. Parents/guardians and childcare workers will be asked for their consent to study participation separately for the following parts of the study: (i) initial questionnaire (paper questionnaire) (ii) further questionnaires (including pseudonymised electronic questionnaires, children interviews), (iii) respiratory sample collection, (iv) blood sampling, (v) guided interviews in a sample of participants. The number of parents/guardians and childcare workers declining participation in any part of the study from the outset will be recorded; if possible, they will be asked to state the reasons for their complete denial of consent. For respiratory sample collection and blood sampling, the consent of both parents/guardians will be required, for the other study parts (questionnaires and interviews) the consent of one parent/guardian will be sufficient. Parents/guardians will be asked to print the informed consent forms and hand in the completed forms in a sealed envelope at the daycare centre. If required, printed versions of the informed consent forms can be provided at the daycare centre. Sealable envelopes pre-addressed to the central study office will also be deposited at the daycare centre for the parents/guardians.

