Together with the informed consent forms, an initial basic questionnaire will be sent out. The informed consent forms will include the option to give consent separately for this part of the study, and the aim is that as many parents/guardians as possible will participate in this initial questionnaire. If consent to other study parts is denied, the initial questionnaire aims to establish the reasons. In addition, the initial questionnaire will include questions on basic sociodemographic data (e.g. age and sex of the index child, number of family/household members, parents' employment status and educational level). For non-participants (denial of consent to participation in central surveillance measures) who nonetheless have provided written consent to participation in this initial basic questionnaire, the data obtained in the initial questionnaire will be completely anonymised. The initial questionnaire will also include questions on participants' opinions regarding the pandemic (personal assessment of the dangers of SARS-CoV-2 and of the sociopolitical response to the pandemic) and their opinions on vaccinations. Persons consenting to participation in this part of the study will be asked to enclose the initial questionnaire in the envelope with the informed consent forms to be handed in at the daycare centre.

Members of the study team will transport the sealed envelopes with the consent forms and, where applicable, the initial basic questionnaires, to the central study office, where the documents will be recorded and archived. For each daycare centre, participant lists for the individual study parts will be created, and each participant will be assigned an ID number (pseudonymisation).

For these daycare centers participating in the main parts of the study, the proportion of potential participants (children, childcare workers) not participating due to missing informed consent will be recorded.

For all participants, written consent to participation in further questionnaires (including children interviews), respiratory sample collection, serological testing (blood sampling at the beginning and end of the study (cf. 6.4.3)) and in guided interviews (in a sample of participants) will be recorded.

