### **Exploratory analyses of potential predictors of acceptance**

- Association between initial consent / drop out regarding respiratory sample collection and:
  - age/ sex of child
  - family/household size
  - employment status, educational level
  - assigned screening module
  - personal assessment of the dangers of a SARS-CoV-2 infection
  - personal opinions on the necessity of social restrictions in response to SARS-CoV-2 infections
  - personal experience of SARS-CoV-2 (e.g. cases of disease or death in family or among friends and acquaintances)
  - personal opinions on child vaccinations

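### For families who refuse sampling, age and sex of the child come only from a voluntary questionnaire, so refusers who return nothing drop out of the exploratory analysis of consent by age and sex

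*Protocol*

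**What the plan says.** Section 7.1 of the protocol plans an exploratory analysis of "Association between initial consent / drop out regarding respiratory sample collection and" a list of predictors that begins with "age/ sex of child". Section 7.2 tests predictors with the chi-squared test and, if numbers allow, multivariable logistic regression, at the 5% level.

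Age and sex are collected in the initial questionnaire: "the initial questionnaire will include questions on basic sociodemographic data (e.g. age and sex of the index child, number of family/household members" (Section 4.2). That questionnaire is voluntary: "The informed consent forms will include the option to give consent separately for this part of the study". It goes back in the same envelope as the consent forms. Non-participants contribute only if they are families "who nonetheless have provided written consent to participation in this initial basic questionnaire, the data obtained in the initial questionnaire will be completely anonymised".

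On other refusers, Section 4.2 plans a count ("The number of parents/guardians and childcare workers declining participation in any part of the study from the outset will be recorded"), reasons where possible, and the proportion per centre without consent. The centre questionnaire in Section 4.1 covers every enrolled child. Its listed items are "number of children cared for, number of childcare workers, number of groups, group sizes, childcare workers per group, number of rooms, overall floor area" and a hygiene checklist.

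For the primary endpoint of modules 1-3, Sections 7.1 and 7.5 keep non-consenters in the denominator as non-successful.

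**The concern.** A family that refuses sampling and returns no questionnaire is counted in the primary rate but has no documented age or sex for the child. It cannot be placed in a table of consent by age or sex. Such a table contains the consenters and only those refusers who chose to answer.

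Two things follow. The consent proportions in the table are too high. And if refusing families of younger and older children, or of girls and boys, differ in how often they return the form, part or all of an apparent association reflects who answered.

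Predictors of acceptance are research question III in Section 1.7, and Section 4.3.2 intends them to identify targets for raising acceptance. An analysis plan can decide how to treat missing covariates, but it cannot recover data never collected. Refusers' questionnaires are also fully anonymised, so they cannot be matched to centre lists later. The remedy therefore belongs in the data collection set out in the protocol.

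**Working it through.** The protocol states no return rate, no consent rate by age and no power for this analysis, so there is no figure of its own to reproduce. The check has two parts.

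**1. Sources of age and sex**

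| Family | Age | Sex |
|---|---|---|
| Consents and gives samples | Questionnaire, and date of birth on the laboratory sample (Section 6.1) | Questionnaire |
| Refuses sampling, returns questionnaire | Questionnaire, anonymised | Questionnaire, anonymised |
| Refuses sampling, returns nothing | None stated | None stated |

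Missing age therefore falls mainly on refusers.

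**2. Size of the possible distortion**

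Let r be the probability that age is known. Then

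observed OR (younger vs older) = true OR × (r[consent, younger] × r[refuse, older]) / (r[consent, older] × r[refuse, younger]).

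If age is known for all consenters, this becomes true OR × r[refuse, older] / r[refuse, younger].

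Inputs from the protocol:
- 375 children, the minimum for modules 1-3 (100 + 100 + 175).
- 30% consent, borrowed from the module 1 acceptance assumption in Section 7.5 because no consent rate is given.

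Assumptions: two equal age bands, no true age effect, independent children, two-sided 5% test, and return rates as shown.

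Each band has 187.5 children: 56.25 consenters and 131.25 refusers.

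- Return 30%/30%: known refusers 131.25 × 0.30 = 39.4 per band. Apparent consent is 56.25/(56.25 + 39.4) = 58.8% against a true 30%. Children missing: 0.70 × 0.70 = 49%. OR = 1.00.
- Return 20%/40%: known refusers 26.25 and 52.5. Apparent consent is 56.25/82.5 = 68.2% and 56.25/108.75 = 51.7%. OR = 0.40/0.20 = 2.0.

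| Refusers' return, younger/older | Apparent consent, younger/older | OR (truth 1.00) | Chance of a significant result | Children missing |
|---|---|---|---|---|
| 30%/30% | 58.8%/58.8% | 1.00 | 5% | 49% |
| 40%/50% | 51.7%/46.2% | 1.25 | 13% | 39% |
| 50%/90% | 46.2%/32.3% | 1.8 | 68% | 21% |
| 20%/40% | 68.2%/51.7% | 2.0 | 63% | 49% |
| 10%/30% | 81.1%/58.8% | 3.0 | 87% | 56% |

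At 37.5% consent, the figure assumed for modules 2 and 3, the odds ratios are the same. The chances of significance for the four unequal pairs, in table order, are 14%, 71%, 64% and 86%.

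Non-return alone does not create an association. If return among consenters varies with age in the same proportion as among refusers, the factor cancels: (0.9 × 0.2)/(0.45 × 0.4) = 1.0.

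With a full count of enrolled children and a complete participant list, r = 1 in every cell. The observed OR then equals the true OR and no child is lost.

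**The case against.** The strongest reply is that little depends on this. The analysis is labelled exploratory, Section 7.2 promises cautious interpretation, and the primary rate keeps all non-consenters in its denominator. Drop-out by age concerns participants and is untouched by silent refusers. The authors also foresaw non-response: a separate consent option, anonymised answers, and a recorded number of decliners. All of this stands and limits the weight of the point. It does not supply age or sex for those who return nothing.

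The Section 4.1 list may also be incomplete. The form itself is not shown, and Section 13.3 describes it by examples, including absence data not listed in 4.1. That is fair, so the finding is about the form as listed.

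A reader might infer more than the documents support:
- That age is known only for families who return the questionnaire. Laboratory samples carry the date of birth, so this is wrong for sampled children.
- That silent refusers are the largest group, or that nearly all returners consent. Neither has a figure behind it.
- That the module 3 denominator cannot be formed. Section 3.1 makes the number of children aged 2 years or older a selection criterion, so centres must supply it.
- That a false age effect is to be expected. It needs return to vary with age differently in refusers and consenters, and nothing in the protocol says that it does or in which direction.

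**Conclusion.** The point holds as a gap in data collection for an exploratory analysis. Silent refusers have no documented age or sex and fall out of the comparison of initial consent by these two predictors. Whenever consenters' data are more complete than refusers', apparent consent is inflated: 58.8% instead of 30% under equal 30% return.

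A false association is possible, not established. The factor on the odds ratio runs from 1.0 with equal return, through 1.25 at 40%/50%, to 2.0 at 20%/40% and 3.0 at 10%/30%. These figures rest on assumed return rates and on age being known for every consenter. The significance figures also rest on the pooled minimum of 375 children in two equal bands. The primary acceptance rate is unaffected. This is a cheap improvement worth making, because the missing data cannot be obtained at the analysis stage.

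**What to change.** - Section 4.1: add to the centre questionnaire one anonymous count of all enrolled children at study start, by broad age band and by sex. Broad bands with separate totals are preferable to single years by sex, which over ages 1-8 would give 16 cells in a centre that may have about 50 children.
- Section 4.2: record age and sex on the participant list for every consenting child. Otherwise a consenter who skips the questionnaire would be misplaced among the non-consenters.
- Section 7.2: compute univariable initial consent and acceptance by age band and by sex over these full counts, per module.
- Section 7.2: report the multivariable model and the other questionnaire-based predictors as conditional on questionnaire return, and show return rates by consent status.

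Cost: a small task for 7-11 centres. Anonymous reporting by centre staff already has a precedent in the absence data of Section 6.1. The tally should be confirmed with the ethics committee. It cannot enter the multivariable model, so the selection remains there and must be stated.
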